#### Data analysis

Analyses will be by intention to treat, including withdrawals and losses to follow-up firstly of all women randomised and then excluding women who lose their options for analgesia. Study groups will be compared in terms of baseline characteristics. As this is a randomised trial, we would anticipate minimal differences in baseline characteristics. If however, important differences are found, these potential confounders will be adjusted for in the analysis of outcomes. For the primary outcomes, the mean score for each measure for each group will be compared using t-tests. If adjustment for confounders is needed a multiple linear regression model will be used. The secondary outcomes will be compared using chi-squared tests of significance for categorical data and t-tests for continuous data. If adjustment for confounding is necessary logistic regression and multiple linear regression will be used respectively.

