**Methods/design:**

We aim to evaluate the effectiveness of a Pain Relief for Labour decision aid, with and without an audio-component, compared to a pamphlet in a three-arm randomised controlled trial. Approximately 600 women expecting their first baby and planning a vaginal birth will be recruited for the trial.

The primary outcomes of the study are decisional conflict (uncertainty about a course of action), knowledge, anxiety and satisfaction with decision-making and will be assessed using self-administered questionnaires. The decision aid is not intended to influence the type of analgesia used during labour, however we will monitor health service utilisation rates and maternal and perinatal outcomes. This study is funded by a competitive peer-reviewed grant from the Australian National Health and Medical Research Council (No. 253635).

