#### Secondary outcomes

##### Service utilisation outcomes

The aim of the decision aid is to assist preference elicitation, and not to influence the direction of the decisions taken. Nevertheless, it is important to collect service utilisation and pregnancy outcome data so we will record and compare the pain relief methods used by women in all arms of the study, as well as recording and comparing rates of pregnancy complications and perinatal outcomes. The latter will be obtained (with informed consent) from the existing computerised obstetric database and include: medical or obstetric complications, induction or augmentation of labour, mode of delivery (vaginal, emergency or planned CS), enrolment to delivery interval, gestational age, birthweight, Apgar scores, perinatal deaths, Neonatal Intensive Care Unit admission and length of stay.

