### 11 statistical issues

#### Sample size

The planned sample size is 600 women, with approximately 200 women to be recruited to each arm of the trial. Based on data for 2001 from the tertiary obstetric hospital where the study will be conducted, about 1500 primiparous women give birth to singleton infants after 36 weeks gestation and 92% use some form of analgesia. We anticipate that at least 50% of women will be both eligible and willing to participate.

The sample size calculations for the trial (significance 0.05, power 0.8) are based on the mean difference in the decisional conflict scale between any two arms of the trial. The effect of decision aids on this scale is documented and effect size data are available [1]. Meta-analysis of four randomised controlled trials comparing a decision aid to a pamphlet and that report a mean difference in decisional conflict gives a pooled mean difference of -4.35, 95%CI -6.8, -1.9 (on a scale ranging from 0 lowest to 100 highest decisional conflict; median standard deviation 13.0) [35-38]. Assuming a mean difference of -4.35 and standard deviation 13.0, we will need about 141 women in each arm of the trial to demonstrate a difference in decisional conflict.

Approximately 20% of primiparous women have a caesarean section (6% before labour and 14% after labour has commenced) [12]. Some of these women will lose their options for analgesia, although some may have extensive use of analgesic agents prior to caesarean section (CS). We plan to conduct an a priori sub-group analysis that excludes women who lose their options for analgesia (defined as a CS planned after randomisation, an emergency CS within 1 hour of arriving in labour or those who receive a therapeutic epidural) as these women may have different satisfaction, anxiety and decisional conflict outcomes. We will inflate the sample size estimate by 20% (from 141 to 169) to ensure sufficient power in the sub-group analyses. A further inflation of 15% for loss to follow-up, gives the final sample size of at least 195 women in each arm of the trial.

If there are no significant differences in outcome for the two decision aid groups (with or without the audio-component), the decision aid groups will be pooled giving two women with the intervention for each woman in the pamphlet group thereby increasing the power to detect differences between the decision aid and the pamphlet.

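### The plan promises to include women lost to follow-up, but the tests it names for the questionnaire outcomes cannot include a woman without a score unless an unstated imputation step comes first

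*Protocol article*

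**What the plan says.** All references are to the protocol article.

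- **Population.** Section 11, Data analysis: "Analyses will be by intention to treat, including withdrawals and losses to follow-up firstly of all women randomised". A second analysis then leaves out women whose choice of analgesia was lost.
- **Primary method.** Same section: "For the primary outcomes, the mean score for each measure for each group will be compared using t-tests". The adjusted version is conditional: "If adjustment for confounders is needed a multiple linear regression model will be used".
- **Source of the primary outcomes.** The abstract says that decisional conflict, knowledge, anxiety and satisfaction "will be assessed using self-administered questionnaires".
- **Timing.** Section 9 places the primary outcome measures on the first questionnaire, before the next antenatal consultation. Section 10 repeats only satisfaction and anxiety at 12–16 weeks postpartum, and section 8 says that this second form is mailed.
- **Baseline data.** Section 6 lists age, brief socio-demographic data, education, state anxiety and information sources. It lists no baseline decisional conflict, knowledge or satisfaction score.
- **Sample size.** Section 11, Sample size, applies "A further inflation of 15% for loss to follow-up" to a calculation with "significance 0.05, power 0.8".
- **Database outcomes.** On pregnancy complications and perinatal outcomes, section 10 says: "The latter will be obtained (with informed consent) from the existing computerised obstetric database".

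**The concern.** A questionnaire score exists only if the woman completes the form. A woman who withdraws, gives birth before the first form or never returns the mailed one has nothing to enter into a comparison of means. The article says that she is included and names no step that would include her. Carrying a baseline value forward is not possible for decisional conflict, knowledge or satisfaction, because none is listed at baseline.

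What is at stake is bias. Women know their allocation (section 9), and two arms receive an aid that takes about 30 minutes while the third receives a pamphlet. The development section reports that women in the pilot's usual-care arm were disappointed to receive no information, and that the pamphlet was introduced partly to limit refusals and loss. The investigators thus saw that retention might depend on what a woman is given. If non-response differs by arm and relates to the score, a comparison of responders is biased, and calling it an analysis of all women randomised would hide that.

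**Working it through.** **1. The plan's own sample size.** Inputs from section 11: difference 4.35, SD 13.0, significance 0.05 (taken as two-sided), power 0.8.

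- n per arm = 2 × (1.960 + 0.842)² × 13.0² / 4.35² = 140.2, rounded up to 141. An exact t-test calculation gives 141.2. The stated 141 is reproduced.
- 141 × 1.20 = 169.2, stated as 169.
- 169 × 1.15 = 194.4, rounded up to 195, as stated.

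**2. Women without a score at 15% loss.**

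- 195 per arm: 0.15 × 195 = 29.25, about 88 of 585 in all.
- 200 per arm: 0.15 × 200 = 30, or 90 of 600 in all.

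**3. Is power the problem?** Power for 4.35 points with SD 13.0:

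| Per arm | All scored | After 15% loss | After 15% loss and the 20% sub-group exclusion |
|---|---|---|---|
| 195 | 91% | 86% (166 women) | 78% (133 women) |
| 200 | 92% | 87% (170 women) | 79% (136 women) |

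In the all-randomised analysis power stays above 80%. The sub-group analysis falls just short of it.

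**4. Possible bias (assumed scenarios).** Let p be the fraction lost in one arm and d the difference between lost women and responders in that arm. Then

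full mean = (1 − p) × responder mean + p × lost mean = responder mean + p × d.

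The responder mean is therefore off by p × d. If lost women in the other arm resemble its responders, the arm difference is off by the same amount.

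| Loss p | d = 0.5 SD (6.5 points) | d = 1 SD (13 points) |
|---|---|---|
| 15% (plan's figure) | 0.975 points, 22% of 4.35 | 1.95 points, 45% |
| 13.3% (26/195, the loss that multiplying by 1.15 actually covers) | 0.87 points, 20% | 1.73 points, 40% |
| 5% (assumed, lighter loss) | 0.33 points, 7% | 0.65 points, 15% |

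The direction depends on the arm. If lost decision aid women are 1 SD worse at 15% loss, an observed −4.35 corresponds to −4.35 + 1.95 = −2.40 among all randomised. If the worse women are lost from the pamphlet arm, the benefit is understated by the same amount. If d and p are equal in both arms, the two terms cancel and the bias is zero.

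**5. Which outcomes are exposed.** Satisfaction and anxiety have two follow-ups, so a woman who misses the mailed form may still have a first score that the analysis can use. Decisional conflict and knowledge have one listed measurement, with neither a baseline nor a later value to draw on. Database outcomes do not depend on returned forms.

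**The case against.** The strongest reply is that nothing in the article says the t-test is run on observed scores only. A t-test names the comparison and leaves open what is done about missing values, so it could follow imputation. The article is condensed, and missing-data rules commonly sit in a full protocol or analysis plan that is not shown. The intention-to-treat sentence heads the analysis of all outcomes, including the database ones, and may mean only that women stay in their allocated arm whatever happens later. **This stands.** A reader might infer that the plan contradicts itself outright, or that a complete-case analysis will be passed off as intention to treat. The text supports neither.

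A reader might also infer that the 15% inflation conflicts with including lost women. It does not. Recruiting extra women protects information, since women without scores add little under any method, and the sample size section does not say that they are excluded.

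The bias figures can fairly be called one-sided. No section supports a 1 SD shift confined to one arm. The first form is completed around a routine visit with research nurse contact, and visits are weekly, so loss on decisional conflict may be well under 15%. This stands too.

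The reply does not remove the point that the article fixes a method as well as a population. Adjustment depends on imbalance being found, and no use is made of the repeated satisfaction and anxiety scores. That is a choice of analysis that can be improved with data the trial already collects.

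**Conclusion.** The point holds in a limited form. For the questionnaire-based primary outcomes, the stated population takes in women whom the named tests cannot use without an imputation step that the article does not mention. The database outcomes are unaffected, and the all-randomised comparison is not short of power.

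The 0.98 to 1.95 points show how much arm-specific loss could matter. They rest on 15% loss, an assumed 0.5 to 1 SD shift and no such shift in the other arm. They are not a property of the plan and should not be read as an expected bias. The point is worth settling before unblinded data are seen, because the outcomes are self-reported by women who know their allocation and a better analysis is available at little cost.

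**What to change.** 1. **Primary model.** Replace the t-test with linear regression on arm, with covariates fixed in advance: baseline state anxiety (at least for the anxiety outcome), age and education. Do not make adjustment depend on imbalance being found. Regression alone does not bring in women without scores; it allows non-response to depend on those covariates.
2. **Satisfaction and anxiety.** Use a mixed model or multiple imputation over the two follow-ups, so that a woman who misses the postpartum form contributes her first follow-up score.
3. **Decisional conflict and knowledge.** Either describe the set as women with available scores, analysed as randomised, or impute by arm and say so. Imputing from age, education and anxiety alone may change little and would not remove bias from loss that depends on the unseen score.
4. **Sensitivity analysis.** For that reason, add a delta-shift analysis by arm: make missing scores worse by a stated amount in one arm at a time, for example 0.25 to 1 SD, and report where the conclusion changes.
5. **Wording.** Say that inclusion of all women randomised applies in full to database outcomes, and how it is met for questionnaire outcomes. Label any t-test on available scores as a complete-case analysis.

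The cost is revised analysis text and modest extra analysis work. No new data and no additional women are needed.

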**Figure 1 F1:**
[figure not shown]
Schema of Pain Relief for Labour Decision Aid trial

Brief baseline data will be collected to assess comparability of the study groups. The baseline assessment will include age, brief socio-demographic data, highest level of education achieved, anxiety as assessed by the state component of the short Spielberger anxiety scale [30], and information sources about labour analgesia.

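### Anxiety has a baseline score, but the primary analysis is an unadjusted t-test and the score is used only if chance imbalance prompts it: precision is lost and the model is chosen on a poor criterion

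*Protocol article*

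**What the plan says.** Section 10 of the protocol article names four primary outcomes: decisional conflict, knowledge (with realistic expectations), anxiety, and satisfaction with the decision. Section 2 makes reduced anxiety the fourth primary hypothesis. Section 12 also uses anxiety, at baseline and follow-up, to pick up adverse effects of the decision aid.

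The baseline assessment in section 6 includes "anxiety as assessed by the state component of the short Spielberger anxiety scale". Section 10 uses the same scale for the outcome. It is taken in the first follow-up questionnaire and again at 12–16 weeks postpartum. Section 6 lists no baseline score for decisional conflict, knowledge or satisfaction.

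On analysis, section 11 states: "For the primary outcomes, the mean score for each measure for each group will be compared using t-tests". On covariates it says that randomisation should leave little baseline difference, and continues: "If however, important differences are found, these potential confounders will be adjusted for in the analysis of outcomes". Multiple linear regression is then used in place of the t-test. The same conditional rule covers the secondary outcomes.

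**The concern.** Two features of the stated analysis deserve a second look.

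The first is precision. A woman's state anxiety at enrolment probably predicts her state anxiety later on the same scale. A t-test on follow-up means makes no use of that. Anxiety is both an efficacy hypothesis and the declared check for harm, so a finding of no difference is likely to be read as reassurance. How reassuring it is depends on the width of the interval. The sample size was set on decisional conflict, and no target difference or power is stated for anxiety.

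The second is the reason for adjusting. In a randomised trial any baseline imbalance arises by chance. A covariate earns its place by predicting the outcome, whether or not it happens to be imbalanced. A trigger based on observed imbalance can leave out a strong predictor that is balanced and bring in a weak one that is not. It also leaves the model open until the baseline table by group has been seen.

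**Working it through.** **The plan's own figure.** Inputs from section 11: "The sample size calculations for the trial (significance 0.05, power 0.8) are based on the mean difference in the decisional conflict scale", and "Assuming a mean difference of -4.35 and standard deviation 13.0, we will need about 141 women in each arm of the trial". With two-sided α (sidedness is not stated, but two-sided reproduces the result), n per arm = 2 × [13.0 × (1.960 + 0.842) / 4.35]² = 140.2, rounded up to 141. The stated inflations also reproduce: 141 × 1.20 = 169.2, taken as 169, and 169 × 1.15 = 194.35, rounded up to 195. These figures concern decisional conflict and are not affected by this point.

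**Precision for anxiety.** Let ρ be the correlation between baseline and follow-up anxiety. The documents do not give it, so a range is assumed. Adjusting for baseline multiplies the residual variance by 1 − ρ², which is equivalent to multiplying the sample size by 1/(1 − ρ²).

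Take 169 women per arm, the plan's number before its allowance for loss to follow-up (close to 200 × 0.85 = 170). The difference detectable by t-test with 80% power, in SD units, is (1.960 + 0.842) × √(2/169) = 0.305. With adjustment it becomes 0.305 × √(1 − ρ²). At a true difference of 0.305 SD, adjusted power is Φ(2.802/√(1 − ρ²) − 1.960).

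| Assumed ρ | 1 − ρ² | Sample-size equivalent | Detectable difference (SD) | Power where the t-test has 80% | Women per arm matching t-test precision |
|---|---|---|---|---|---|
| 0.3 | 0.91 | ×1.10 | 0.291 | 84% | about 154 |
| 0.5 | 0.75 | ×1.33 | 0.264 | 90% | about 127 |
| 0.6 | 0.64 | ×1.56 | 0.244 | 94% | about 108 |
| 0.7 | 0.51 | ×1.96 | 0.218 | 97.5% | about 86 |

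The 80% is only a reference point, because the protocol sets no target difference for anxiety.

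**Type I error of the conditional rule.** The protocol does not say what counts as an important difference, so a baseline p<0.05 is assumed. Under randomisation that trigger fires for a given covariate in about 5% of two-arm comparisons, so the precision gain is forgone in about 95%. A simulation under the null used 10,000 trials with 169 women per arm and normal scores:

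| Strategy | ρ = 0.5 | ρ = 0.7 |
|---|---|---|
| Always t-test | 5.1% | 5.1% |
| Always ANCOVA | 5.0% | 4.8% |
| ANCOVA only if baseline p<0.05 | 4.4% | 3.8% |
| Either test significant (free choice) | 7.4% | 8.2% |

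With ρ positive, false rejections by the t-test tend to occur in trials with a large baseline imbalance. In those trials the rule switches to the adjusted test. In the rest the t-test keeps a standard error that is too wide given near-balance. The fixed-trigger rule therefore rejects somewhat too rarely.

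**The case against.** The unadjusted t-test is valid and unbiased under randomisation, and it matches the sample size calculation, which uses an unadjusted SD. The sized outcome loses no planned power. That stands, so this is a point about efficiency and the basis of model choice, not about bias.

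The size of the gain rests on an assumed correlation. The scale measures a state, and the second follow-up falls on the other side of childbirth, so ρ may well be lower at 12–16 weeks. At ρ = 0.3 the gain is only about 10%. That stands too, and is why a range is given.

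A reader might infer that the conditional rule yields two rival primary results or inflates false positives. The text does not support this. It selects one model, and the selection depends on baseline comparability rather than on outcome results. The 7.4% and 8.2% figures need an analyst who freely picks the better of two p-values, which the protocol does not allow for.

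A reader might also say that baseline anxiety is ignored. It is not: the protocol wants changes in anxiety documented, and baseline anxiety could enter the regression if imbalanced. Its use is conditional.

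The missing threshold for importance and the missing covariate list may stand in an analysis plan that is not shown, and are not criticised here. The t-test default and the imbalance trigger are different. They are stated rules, and an analysis plan faithful to this text would inherit both.

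**Conclusion.** The point holds in a limited form. For anxiety, the stated primary analysis discards a share ρ² of the outcome variance that data already collected could remove. That is worth about 10% to 56% more women for assumed ρ between 0.3 and 0.6, possibly less postpartum. The imbalance trigger is a poor basis for choosing the model for any outcome. Under an assumed fixed p<0.05 trigger its effect on error is mild conservatism (4.4% at ρ = 0.5 and 3.8% at ρ = 0.7).

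The documents do not show bias, inflated type I error or a power shortfall. Nor does the precision argument extend to decisional conflict, knowledge or satisfaction. These have no listed baseline score, and nothing in the protocol shows that age, education or baseline anxiety predicts them.

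**What to change.** In the Data analysis section:

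- Make linear regression (ANCOVA) with the baseline short Spielberger state score as covariate the primary analysis of anxiety, at the first follow-up and at 12–16 weeks postpartum. Report the unadjusted t-test as a sensitivity analysis.
- Remove the rule that adjusts when important baseline differences are found. Replace it with a statement that any covariates are fixed before data by study group are seen and are chosen for expected prognostic value.
- For decisional conflict, knowledge and satisfaction, the unadjusted comparison may stay primary. Any covariates for them should be chosen in advance on the same principle.
- Keep the descriptive baseline table, but give it no role in choosing the model.

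The cost is wording only. No additional data, visits or women are needed and the sample size does not change. If ρ proves low, adjusting for one covariate costs almost nothing with about 169 women per arm.

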### 10 outcome measures

#### Primary outcomes

The primary outcomes of this study will be:

*Decisional conflict *(uncertainty about which preference to choose) will be assessed by the Decisional Conflict Scale which has established reliability, good psychometric properties and is short (16 items) [31]. It has been used to evaluate a range of decision aids [1].

*Measures of knowledge and realistic expectations *about labour analgesia options and the benefits and risks of these options will be specific to this project. Thus we will need to develop, and test these measures as part of the project.

*Anxiety *will be measured by the state component of the short Spielberger anxiety scale which has been extensively used and validated [30,32]. We do not anticipate the decision aid will increase women's anxiety but it is important to document any changes in anxiety associated with the decision aid.

*Satisfaction *with analgesia decisions will be assessed using the Satisfaction with Decision Scale – a very brief six item scale with high reliability was developed specifically to assess satisfaction with health care decisions [33].

Satisfaction with the decision and anxiety will be measured again at 12–16 weeks postpartum. This interval was chosen to avoid the potential bias arising from questioning women still in the hospital who may feel a disloyalty to their caregivers by a critical appraisal and whose opinions have been shown to be more positive and short-lived than those obtained further out from the birth itself [34]. At that time we will also ask about exposure to the decision aid (to assess contamination), support during labour and use of pain relief methods prior to hospital admission. These issues will be further explored in the sample selected for in-depth interview.

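### Four co-equal primary outcomes are each tested by t-tests with no stated error control, so a false primary result for decision aid versus pamphlet has a chance of about 20–24% even under the plan's pooling rule

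*Protocol article*

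**What the plan says.** The Abstract (Methods/design) lists the outcomes: "The primary outcomes of the study are decisional conflict (uncertainty about a course of action), knowledge, anxiety and satisfaction with decision-making". Section 2 (Hypotheses) gives each its own primary hypothesis, and section 10 repeats the list without ranking. Section 10 words the knowledge item as "Measures of knowledge and realistic expectations", and adds that "Satisfaction with the decision and anxiety will be measured again at 12–16 weeks postpartum". Section 3 sets three arms: pamphlet, decision aid with audio, decision aid without audio.

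Under Sample size in section 11, "The sample size calculations for the trial (significance 0.05, power 0.8) are based on the mean difference in the decisional conflict scale", taken between any two arms. The result is "Assuming a mean difference of -4.35 and standard deviation 13.0, we will need about 141 women in each arm of the trial". The same section says the two decision aid arms will be pooled against the pamphlet if they do not differ significantly.

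Under Data analysis, "For the primary outcomes, the mean score for each measure for each group will be compared using t-tests". All women randomised are analysed first, and the analysis is then repeated without women who lose their analgesic options.

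Section 9 bears on timing: it identifies the first questionnaire, completed before the next antenatal consultation, as the one that carries the primary measures.

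**The concern.** Each of the four hypotheses can be declared supported by its own t-test, and no outcome is said to decide whether the decision aid works. If every test uses 0.05, the 5% applies to a single test and not to the set of primary conclusions. A trial of an ineffective aid would then have a substantial chance of reporting at least one significant primary result. With mixed results, the plan gives no basis for saying whether the trial succeeded.

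Only decisional conflict has a stated effect, standard deviation and power. The unadjusted 0.05 is also built into the sample size, so a later split of alpha would use up power that the trial was planned to have.

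**Working it through.** **Inputs.** From the article: four primary outcomes; three equal arms of about 200; difference 4.35, SD 13.0, significance 0.05, power 0.8; 15% loss to follow-up; the conditional pooling rule. Assumed: two-sided 0.05 for every t-test (the article gives 0.05 only in the sample-size paragraph); equal correlation of 0 to 0.5 between outcomes; the pooling rule applied outcome by outcome, also at 0.05.

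**1. The plan's own figure.** n per arm = 2 × (1.96 + 0.842)² × (13.0/4.35)² = 140.2, so 141. This matches the article and confirms one two-sided comparison at an unadjusted 0.05. A one-sided test would give 111. The inflations also follow: 141 × 1.20 = 169.2 and 169 × 1.15 = 194.4, against at least 195 stated.

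**2. Chance of at least one false result on one outcome.**
- All three pairs: 12.2%, by simulation with arms shared between pairs.
- Two pamphlet pairs: the two test statistics correlate 0.5 through the shared pamphlet arm, which gives 9.07%.
- Pooling rule (test audio versus no audio; if not significant, test the pooled aid against the pamphlet; otherwise test each aid arm against the pamphlet), counting aid versus pamphlet only: about 6.6%, by simulation.

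**3. Four outcomes.** With independent outcomes the chance is 1 − (1 − p)⁴:
- three pairs: 1 − 0.878⁴ = 40.6%
- two pamphlet pairs: 1 − 0.9093⁴ = 31.6%
- pooling rule: 1 − 0.934⁴ = 23.9%

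Simulation under no effect on any outcome gives the values with correlated outcomes:

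| What counts as a false primary result | Correlation 0 | 0.3 | 0.5 |
|---|---|---|---|
| Aid versus pamphlet, pooling rule | 24.0% | 22.4% | 20.3% |
| Same, false benefit only | 12.5% | 11.3% | 10.2% |
| Two unpooled pamphlet pairs | 31.7% | 29.7% | 26.8% |
| All three pairs, including audio versus no audio | 40.6% | 38.1% | 34.6% |

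Even if the aid arms were always pooled, four independent outcomes alone would give 1 − 0.95⁴ = 18.5%. Most of the excess therefore comes from the number of outcomes, not the number of arms.

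**4. What a later alpha split would cost.** At 0.05/4 the same formula gives 200 evaluable women per arm for 80% power, before either inflation. With 170 evaluable per arm (200 less 15%), power for one pair on decisional conflict falls from 87% at 0.05 to 72% at 0.05/4.

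**5. Power of a single primary test.** For both aid arms against the pamphlet, power = Φ(4.35 / [13.0 × √(1/n₁ + 1/n₂)] − 1.96).
- 141 versus 282: Φ(3.244 − 1.96) = 90.0%
- 170 versus 340: Φ(3.562 − 1.96) = 94.5%

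**The case against.** The best defence is that the article is condensed, that an analysis plan not shown here may handle multiplicity, and that 0.05 is stated only for the sample size. That limits what can be said about the level used in each t-test, and it is why 0.05 appears above as an assumption. It does not remove the point. The equal rank of four outcomes is fixed in this document, and the sample size already spends the full 0.05 on one of them.

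A second defence is that success might require all four outcomes. The article does not say so. Assuming 80% power on each and independence, joint power would be 0.8⁴ = 41%.

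Several stronger readings are tempting, and the document does not support them:
- **35–41% as the headline.** This counts audio versus no audio as a primary claim. The hypotheses in section 2 concern the decision aid, and the pooling rule narrows the comparison further.
- **No primary time point.** Section 9 ties the primary measures to the first questionnaire, and section 10 presents the 12–16 week measures as repeats. Counting six outcome-by-time endpoints is therefore not justified, although the repeats do stand under the primary heading.
- **A doubled count for the exclusion analysis.** Section 11 already calls it a sub-group analysis and places it second.
- **Five outcomes.** Only the Specific Aim lists expectations separately. Section 10 joins them to knowledge.
- **A chance benefit is likely.** False benefit alone is about 10–12.5% under the pooling rule.
- **The other outcomes are unpowered.** No effect is stated for them, but 141 per arm gives about 80% power for 0.33 SD on any scale, and the sizing covers any pair of arms.

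**Conclusion.** The concern holds in its narrower form. Four co-equal primary outcomes are tested separately, and the trial is sized at an unadjusted 0.05 on one of them. For the question that the hypotheses ask, decision aid versus pamphlet, the chance of at least one false two-sided primary result is about 20–24% under the pooling rule and about 27–32% without it. Both are well above 5%.

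These figures assume 0.05 per test, no true effect on any outcome, and correlations of 0 to 0.5. At a correlation of 0.7 the pooling-rule figure is still 17%. The conclusion does not depend on counting the audio contrast, the late repeats or the exclusion analysis.

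**What to change.** Amend section 10 and both parts of section 11:

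- **Single primary test.** Decisional conflict at the first follow-up questionnaire, both decision aid arms together against the pamphlet, all women randomised, two-sided 0.05. This is the outcome already used for sizing and the time point that section 9 already implies.
- **Behind the gate.** If that test succeeds, test knowledge, satisfaction and anxiety at the first questionnaire, either in a stated fixed order or by Holm across the three. Choose one of the two in advance.
- **Anxiety.** Report it with its confidence interval whatever the gate, because sections 10 and 12 also use it to document adverse effects.
- **Supportive analyses.** State that the 12–16 week repeats and the analysis excluding women who lose their options are supportive.
- **Audio versus no audio.** Report it as a separate prespecified comparison with a confidence interval. It is the reason for having two decision aid arms and should stay visible, but it should no longer determine how the primary comparison is formed.

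This is a change of wording and needs no extra women. The cost is that knowledge, satisfaction and anxiety cannot be claimed as confirmed if decisional conflict fails. Under a fixed order, an outcome also cannot be claimed if one ranked above it fails.
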